### Interventions

2.3

#### Interventions for each group with sufficient details

2.3.1

The clinical trial will be divided into three parts as follows:

**Arm 0**: Patients in this group won't receive any special treatment and will continue to receive their usual care.

**Arm 1:** The principal investigator will exclusively provide educational intervention to COPD patients in this group. The intervention will involve disease education, proper medication usage, and lifestyle modifications, which will include dietary and exercise recommendations. The medications prescribed by their physician will continue to be given to the patients in this group.

**Arm 2:** The standard COPD GOLD guidelines will be followed to administer pharmaceutical care as follows:Step 1The recommended standard diagnostic procedures outlined in the guidelines will be used for patients to undergo diagnosis. The guidelines will categorize them into the appropriate GOLD stages based on their diagnosis. In addition, there will be monitoring to detect any potential co-morbidities.Step 2Pharmacological treatment will be given based on the diagnosed stage of the disease, as well as non-pharmacological interventions like flu vaccines.Step 3Educational intervention in the form of a 30-min face-to-face patient counseling session will also be provided, following the guidelines as mentioned in the first arm.

#### Study activities

2.3.2

1.Patients will be registered at the outpatient department of Holy Family Hospital in Rawalpindi, Pakistan, with the principal investigator and a physician administering the interventions.2.Interventions will be administered to both groups when patients are enrolled.3.Patients will be asked to assess their adherence during follow-up visits every two months. Patients interviews and a review of their prescriptions and medications will be used to evaluate treatment compliance.4.Interventions will be given only once, however, the final evaluation which include, the disease state, quality of life, and the number of acute exacerbations during the study period, will be conducted after six months.

#### Criteria for discontinuing or modifying allocated interventions for a given trial participant

2.3.3

The treatment regimen will be modified if the patients' condition worsens, and the number of emergency visits exceed the specified threshold.

#### Strategies to improve adherence to interventions

2.3.4

After enrollment, there will be in-person reminder session that will be conducted every two months during each follow-up appointment. The following components will be covered during these sessions.a)Emphasizing the significance of adhering to the study guidelines regarding medication adherence, providing instructions on medication administration, including dosage regimen and storage, impact of medication adherence and guidance on dose adjustment if a dose is missed.b)Subsequent sessions will be held during follow-up visits. Participants will be evaluated objectively and subjectively to assess their disease status and quality of life during these sessions. A brief discussion will be held on the reasons for missed doses and simple strategies to enhance adherence. The discussion will focus on linking intervention adherence to daily routines and considering the impact on health-related quality of life and the frequency of emergency visits.

#### Outcomes

2.3.5

Primary outcome [1]:

Quality of life assessed using the St. George's Respiratory Questionnaire.

Timepoint [1]:

After 24 weeks/6 months of commencement of intervention the outcomes will be assessed.

Primary outcome [2]:

No. of acute exacerbation or No. of emergency hospital visits will be counted from patients’ medical record (prescriptions, lab reports etc.)

Timepoint [2]:

24 weeks/6 months after interventions.

Primary outcome [3]:

Spirometry will be used to assess disease progression. Forced Expiratory Volume (FEV1) will be measured for 1 s measured before and after intervention to study the impact of interventions.

Timepoint [3]:

The disease will be assessed after 24 weeks or 6 months of intervention.

Secondary outcome [1]:

The comparison will involve comparing the number of acute exacerbations (no. of emergency visits) and mortality rate of all study groups.

Time point [1]:

After 1 year of interventions.

### Participant timeline

2.4

See Fig. 1: Patient timeline according to the SPIRIT guideline following SPIRIT guideline 2013.a.Measures to enhance the patients' adherence to the clinical trial:

**Fig. 1 fig1:**
[figure not shown]
Patient timeline according to the SPIRIT guideline following SPIRIT guideline 2013.

Each patient's drug quantity and date of drug ingestion will be documented. During each visit, the patients will be expected to talk about the missing medications, which will be documented by the principal investigator.b.Assessment of Clinical trial progress time:

The participants will be scheduled for an assessment of their adherence to the interventions, particularly at the two-month follow-up intervals. Data will be collected about patient quality of life, the number of acute exacerbations, and disease progression during these assessments. Spirometry tests will be conducted during each visit to monitor these parameters.

### Sample size estimation and recruitment target

2.5

The primary goal of this feasibility study is to gather eligibility and recruitment data to provide a precise estimate of the required sample size for a future trial. To achieve the specified participant count, a realistic recruitment strategy will be utilized, based on findings from previously published clinical trial studies. We anticipate enrolling 120 patients for this study, and we have a contingency plan that will cover a dropout rate of 5 %–10 %.

### Recruitment

2.6

The principal investigator will undertake the recruitment of participants from Holy Family Hospital in Rawalpindi, Pakistan, following the screening, randomization, and follow-up process outlined in Fig. 2 of the CONSORT Flow Diagram. Participants in the trial will be given a brief overview of the trial's objectives, methodologies, potential side effects, and advantages. The following two primary strategies will be implemented to ensure an adequate number of participants during the enrollment phase, which will last for 24 weeks.1.Disseminating recruitment materials in prominent hospital locations, including the outpatient lobby and ward entrances.2.In cases where potential participants are identified within the hospital wards, either the hospital's inpatient staff or the principal investigator will approach them to gauge their interest in participating

**Fig. 2 fig2:**
[figure not shown]
CONSORT Flow Diagram of screening, randomization and follow-up.

### Methods: assignment of interventions (for controlled trials

2.7

A.**Sequence Generation:** Participants will be assigned randomly to either the control or experimental groups, following a 1:1:1 allocation ratio determined by a computer-generated randomization schedule.B.**Confidentiality:** The personal medical records of the subjects will only be granted access to by the principal investigator of the clinical trial.

The principal investigator will also be required to sign an “Investigator Statement” or “Confidentiality Agreement” affirming their commitment to maintaining confidentiality. Data handling will strictly adhere to a “data anonymization” approach, ensuring that any information that could reveal the specific identity of the subjects is excluded. The allocation sequence will be generated by the principal investigator and the hospital's health care team, participants will be enrolled, and they will be assigned to interventions.

### Methods: data collection, management, analysis

2.8

#### Data collection methods

2.8.1

A.**Data collection methods:** Prior to enrolling patients into either the control or experimental groups, a baseline assessment will be conducted to evaluate the patients' disease status, including co-morbidities, quality of life and their knowledge about the disease. Pre-validated questionnaires will be utilized in this assessment. To compare the interventional groups and control group, the same parameters mentioned above will be assessed at each follow up.B.**Retention**: To ensure their continued participation in this study, patients will be given medications as well as other health care services.

##### Data management

2.8.1.1

The principal investigator will use pre-validated questionnaires to collect all the data in collaboration with the patients' pathology records. This data will be electronically recorded for future analysis and interpretation. Data collection will happen both during the baseline and after each follow-up assessment. The participant files will be systematically arranged in numerical order and stored securely in an easily accessible location. Following the conclusion of the study, the participant files will be kept in storage for a duration of 3 years.

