## Confidentiality

The purpose of getting personal information is to adhere the patient in the clinical trial and once the study will be completed each patient will be given a specific code hiding his/her original identification.

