## Access to data

Only the principal investigator and primary sponsor will have the access to the data until it will be published.

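### The investigator who delivers the education also collects the SGRQ data and counts events knowing the arm; self-completion before counselling, coding at enrolment and coded analysis would reduce this exposure

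*Protocol article*

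**What the plan says.** The roles are spread over several sections of the protocol article.

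- **Allocation (2.7):** "The allocation sequence will be generated by the principal investigator and the hospital's health care team".
- **Intervention (2.3.1, Arm 1):** "The principal investigator will exclusively provide educational intervention to COPD patients in this group". Arm 2 receives the same kind of education as its third step, and 2.3.2 describes the study as run "with the principal investigator and a physician administering the interventions".
- **Data collection (2.8.1.1):** "The principal investigator will use pre-validated questionnaires to collect all the data".
- **Setting of the quality-of-life assessment (2.3.4):** "Participants will be evaluated objectively and subjectively to assess their disease status and quality of life during these sessions". The same item then provides for a discussion of missed doses and of how adherence bears on quality of life and emergency visits.
- **Records (2.7 B):** "The personal medical records of the subjects will only be granted access to by the principal investigator of the clinical trial". Primary outcome 2 in 2.3.5 is counted from those records.
- **Coding (Confidentiality section):** "once the study will be completed each patient will be given a specific code". Section 2.7 B, however, promises that data handling will be anonymized.
- **Data access (Access to data section):** "Only the principal investigator and primary sponsor will have the access to the data until it will be published".

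The SGRQ is primary outcome 1 in 2.3.5. The article does not say whether the patient fills it in or the investigator reads it out.

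**The concern.** The SGRQ is a patient-reported measure. If the person who gave the counselling also collects the answers, and does so in a session about adherence and its benefits, two influences can favour the active arms: the way questions are put or clarified, and the patient's wish to give the counsellor a good report. The control arm has had no such education, so the influence need not be equal across arms.

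The event count is exposed to a lesser degree. Its only reader knows the arm, and deciding whether an entry in the records counts can take some judgement.

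A shift of this kind cannot be told apart from a treatment effect afterwards. The regression models in 2.8.2 adjust for patient characteristics, not for how an answer was obtained. The exposure comes from roles that the article assigns, so it is not just a matter of detail left to a fuller protocol.

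**Working it through.** **Step 1: trace the roles.** Sections 2.7, 2.3.1, 2.3.2 and 2.8.1.1 name the same person for generating the allocation (with the hospital team), delivering the education and collecting all questionnaire data. Section 2.7 B makes that person the only one with access to the records. An assessor in this position knows the arm.

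**Step 2: place the SGRQ within the visit.** Section 2.3.4 puts the quality-of-life evaluation inside the two-monthly sessions, and 2.4 confirms that these data are collected at those visits. The evaluation is mentioned before the discussion, but no order is fixed. From the second follow-up on, an earlier session has in any case taken place. The section does not say whether control patients attend the same sessions. If they do, only the part of the influence that differs between arms biases the comparison.

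**Step 3: compare the coding statements.** Anonymized handling (2.7 B) and codes given only after completion (Confidentiality section) leave it unclear how data are identified while outcomes are collected and analysed.

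**Step 4: illustrate the size.** The planned 120 patients have no stated effect size, SD, alpha or power behind them, so that figure cannot be reproduced. The point does not depend on it. Inputs from the documents are N = 120 (2.5), 1:1:1 allocation (1.2), dropout of 5% to 10% (2.5) and a t-test for continuous outcomes (2.8.2).

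- Per arm: 120 / 3 = 40. If 120 is the number enrolled, 40 x 0.95 = 38 or 40 x 0.90 = 36 complete.
- Assumptions: two-sided alpha 0.05, no true effect, and a total bias b of 0.1 to 0.3 SD in favour of one active arm.
- The t statistic is then noncentral t with 2n - 2 degrees of freedom and noncentrality b / sqrt(2/n). The error rate is the probability that it falls outside the two-sided 5% limits.

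| b (SD) | noncentrality, n = 40 | error rate, n = 40 | noncentrality, n = 36 | error rate, n = 36 |
|---|---|---|---|---|
| 0.1 | 0.447 | 7.3% | 0.424 | 7.0% |
| 0.2 | 0.894 | 14.3% | 0.849 | 13.3% |
| 0.3 | 1.342 | 26.3% | 1.273 | 24.1% |

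For scale, 40 per arm detects (1.960 + 0.842) x sqrt(2/40) = 0.63 SD with 80% power. A shift of 0.2 SD is about a third of that (0.2 / 0.63 = 0.32).

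These rates describe an assumed total bias in one comparison. They do not show how much of it the fix would remove, and the same table would fit any open-label trial with a patient-reported outcome.

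**The case against.** **The mode of administration is not stated.** Using questionnaires to collect data is compatible with patients filling them in and handing them over, and an article may leave that to the full protocol. This stands as far as it goes: the investigator reading the items aloud is an inference. But the article does place the evaluation inside the counsellor's session. If self-completion is already the practice, one sentence settles the matter.

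**The order may already be right.** In 2.3.4 the evaluation is mentioned before the discussion. This stands in part. The requested order agrees with the text but is not fixed by it.

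**Event counts leave less room for judgement.** Sections 2.2 and 2.3.5 (secondary outcome) equate exacerbations with emergency visits, which can largely be read off the records. This stands, and the main weight is therefore on the SGRQ.

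**Stronger readings.** A reader might infer that the plan rules out any masked count or check. The documents do not support that. The sole-access sentence is a confidentiality rule, the same section promises anonymized handling, and the sponsor also has access to the data. A reader might also infer that a masked abstractor from the existing hospital team would solve the problem at no cost. That team helps generate the allocation, a free and independent member is an assumption, and the prescriptions used as a source may reveal the arm. It would in effect be an added assessor, with wider access to identifiable records.

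**The trial is exploratory.** Sections 1.2 and 2.5 describe it as exploratory and as a feasibility study. That lowers the stakes, but 2.8.2 plans comparative tests and the Discussion expects conclusions on the impact of both interventions.

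**Conclusion.** The concern holds in a limited form. By the article's own assignment of roles, the SGRQ is open to interviewer and counselling influence, and the event count rests on one unmasked reader with sole access to the records. The statements on anonymization and on the timing of codes need to be reconciled.

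The direction of any bias is plausible but not shown, and its size cannot be derived from the documents. If the total were 0.1, 0.2 or 0.3 SD, the error rate per comparison would be about 7%, 13-14% or 24-26% instead of 5%. Patients know whether they were counselled, so their own reporting bias would remain after any change in who collects the form. The removable share is smaller than the total and unknown. The point is still worth acting on, because it concerns a primary outcome and the remedy is cheap.

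**What to change.** - **2.8.1.1 and 2.3.4:** state that at each visit the patient completes the SGRQ alone, before any counselling or reminder discussion and without help from the investigator. The Informed consent section limits enrolment to patients able to read written instructions, which makes this feasible. It attributes that requirement to the inclusion criteria, but 2.2 does not list it, so add it there.
- **Confidentiality section and 2.7 B:** assign the study code at enrolment, and make the two statements agree on when and how data are anonymized.
- **2.8.2:** run the comparative analysis with arm labels coded until the results are fixed. This guards the choices made in analysis. It does not undo influence at data collection, and the masking is only partial if the analyst is the person who collected the data.

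**Cost:** changes of wording and a small change in visit order, with no added staff. A few more SGRQ items may be left unanswered. Section 1.2 describes the trial as ongoing, so record the date from which the new order applies. The event count would still be made by an unmasked reader, and the report should say so.

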#### Statistical methods – outcomes

2.8.2

The intervention groups will be compared to the control group in our primary analyses. The chi-squared test will be used to evaluate binary outcomes, while continuous outcomes will be evaluated using the T-test. In order to analyze subgroup, regression techniques will be employed and appropriate interaction terms (i.e., subgroup × treatment group) will be incorporated. The use of logistic regression for binary outcomes and linear regression for continuous outcomes will result in multivariable analyses. The residuals will be analyzed to assess model assumptions and goodness-of-fit.

We will utilize Kaplan-Meier survival analysis for time-based endpoints like mortality, followed by multivariable Cox proportional hazards modeling to adjust for baseline variables. During the statistical analysis phase, SPSS software version 22 will be used to code and enter the for preliminary and 6-month assessments.

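### The primary t-test for SGRQ and FEV1 names no baseline covariate although both are measured at baseline; a baseline-adjusted analysis would gain precision at no cost

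*Protocol article*

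**What the plan says.** Section 2.8.2 of the protocol article sets the frame with "The intervention groups will be compared to the control group in our primary analyses" and then names the method: "continuous outcomes will be evaluated using the T-test".

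Two of the three primary outcomes in section 2.3.5 fall under that rule, both assessed at 24 weeks: "Quality of life assessed using the St. George's Respiratory Questionnaire", and FEV1, which is "measured before and after intervention to study the impact of interventions".

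Both have a baseline value. Section 2.8.1 places an assessment of disease status and quality of life before assignment to groups and adds that "the same parameters mentioned above will be assessed at each follow up". Visits are two-monthly (section 2.3.2), and section 2.4 states: "Spirometry tests will be conducted during each visit to monitor these parameters".

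Section 2.8.2 also contains: "The use of logistic regression for binary outcomes and linear regression for continuous outcomes will result in multivariable analyses". It names no covariates for these models and does not call them primary. Adjustment for baseline is written out only for time-based endpoints such as mortality: "multivariable Cox proportional hazards modeling to adjust for baseline variables".

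**The concern.** In a randomised comparison, the baseline value of a continuous outcome usually predicts its later value. An analysis that leaves it out carries avoidable residual variance and has wider intervals. If the test is on the 24-week value, it also leaves in the estimate whatever baseline difference arose by chance.

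At about 40 patients per arm both effects matter. The article calls the trial exploratory (section 1.2) and a feasibility study meant to inform a later sample size (section 2.5), so the precision of the estimated differences is a large part of what it can deliver. The article has also fixed the method: it names the test and attaches it to the primary comparisons. The point is therefore that a stated method can be replaced by a better one, not that a detail is missing.

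**Working it through.** **Inputs from the article.** 120 patients (section 2.5) at 1:1:1 (section 1.2) give 120/3 = 40 per arm. Dropout of 5% to 10% is mentioned in section 2.5, without saying whether it comes out of the 120. If it does, completers are 40 × 0.95 = 38 to 40 × 0.90 = 36 per arm. The article gives no alpha, power, effect size, SD or correlation, so there is no planned power to reproduce.

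**Assumptions.** Two-sided 5%, 80% power, pairwise arm versus control, 36 completers per arm, equal variance at baseline and 24 weeks, and r = 0.5, 0.6, 0.7, 0.8. Results are in SD units because no SD is given.

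**Variance of the between-arm difference**, relative to a t-test on the 24-week value:
- t-test on the 24-week value: 1
- t-test on change from baseline: 2(1 − r)
- ANCOVA with baseline as covariate: 1 − r²

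**Starting point.** By the noncentral t distribution, the detectable difference for a t-test on the 24-week value is 0.670 SD with 36 per arm (0.634 SD with 40).

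**Against a t-test on the 24-week value.** Variance saved = r²; detectable difference = 0.670 × √(1 − r²); equivalent n per arm = 36/(1 − r²).

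| r | variance saved | detectable difference with ANCOVA | equivalent n per arm |
|---|---|---|---|
| 0.5 | 25% | 0.58 SD | 48 |
| 0.6 | 36% | 0.54 SD | 56 |
| 0.7 | 49% | 0.48 SD | 71 |
| 0.8 | 64% | 0.40 SD | 100 |

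**Against a t-test on change.** Variance ratio = (1 − r²)/(2(1 − r)) = (1 + r)/2, so variance saved = (1 − r)/2; equivalent n per arm = 36 × 2/(1 + r). The detectable difference of the change-score test is 0.670 × √(2(1 − r)).

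| r | variance saved | detectable difference, change-score test | equivalent n per arm |
|---|---|---|---|
| 0.5 | 25% | 0.67 SD | 48 |
| 0.6 | 20% | 0.60 SD | 45 |
| 0.7 | 15% | 0.52 SD | 42 |
| 0.8 | 10% | 0.42 SD | 40 |

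The ANCOVA factors ignore the one degree of freedom spent on the covariate, which is negligible here.

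**Chance imbalance.** Section 2.7 describes no stratification. Taking allocation as unstratified, the baseline difference between two arms of 40 has standard deviation √(2/40) = 0.22 SD. The chance that it exceeds 0.3 SD in either direction is P(|Z| > 0.3/0.224 = 1.34), about 18%. A t-test on the 24-week value carries r times the imbalance into the estimate: at r = 0.7 and an imbalance of 0.3 SD, 0.7 × 0.3 = 0.21 SD.

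**The case against.** **The test may already use the baseline.** The article does not say which value enters the t-test. The before-and-after wording for FEV1 leaves a between-arm t-test on change open, and that test uses the baseline. This stands. It is why the gain is shown for both readings, and the difference is greatest at high r, where the 24-week-value reading looks worst. A reader might infer that the plan certainly discards a large part of its precision. The documents support neither the certainty nor the size, because they state neither the value tested nor r.

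**Regression is already planned.** It is, but its covariates are unnamed and it is not primary, so it does not settle the primary result.

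**The two-monthly values.** A reader might think that ignoring months 2 and 4 is itself a large loss. With complete data those visits add little to the 24-week contrast once baseline is in the model; they help mainly when 24-week values are missing. Nor do the documents show that patients who miss the last visit would be dropped: the article states no missing-data rule, which is commonly left to the analysis plan.

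**Before-and-after testing within arms.** The FEV1 wording, together with eligibility based on recent exacerbations, might suggest that improvement within an arm will be credited to the intervention when it is regression to the mean. The documents do not support this. Section 2.8.2 makes the primary comparisons between arms, section 2.8.1 gives the same purpose for the follow-up assessments, and a concurrent randomised control removes that bias.

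**Seriousness.** A t-test is valid under randomisation, the trial is exploratory, and no stated power is contradicted. All of this is right and limits the point to efficiency.

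**Conclusion.** The point holds as a recommendation to improve a stated method. The primary between-arm test for SGRQ and FEV1 names no baseline covariate although the baseline values are collected, and no other analysis in section 2.8.2 is said to contain the baseline outcome and be primary.

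The size depends on which t-test is meant and on r. Under the assumptions listed, the variance gain for r from 0.5 to 0.8 rises from 25% to 64% if the t-test is on the 24-week value, and falls from 25% to 10% if it is on change. With 40 completers per arm instead of 36, these percentages are the same and the starting detectable difference is 0.63 SD. ANCOVA is, in large samples, never less efficient than either t-test, so the recommendation does not depend on knowing r. The open choice between final value and change is a further reason to fix the text.

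**What to change.** In section 2.8.2, make the primary analysis of SGRQ and FEV1 an ANCOVA of the 24-week value on arm, with the baseline value of the same outcome as covariate. Report each intervention-versus-control difference with a 95% CI. Keep the t-test as a sensitivity analysis and state whether it is on the 24-week value or on change.

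A mixed model over months 2, 4 and 6 with the baseline value is an acceptable alternative, useful mainly if 24-week values are missing.

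The cost is a change of wording, made before the data are analysed. All the values needed are already planned to be collected, and neither the sample size nor the visit schedule changes.
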